## Abstract

**Background:**

The objectives of this smoking cessation study among hospitalized smokers are to: 1) determine provider and patient receptivity, barriers, and facilitators to implementing the nurse-administered, inpatient Tobacco Tactics intervention versus usual care using face-to-face feedback and surveys; 2) compare the effectiveness of the nurse-administered, inpatient Tobacco Tactics intervention versus usual care across hospitals, units, and patient characteristics using thirty-day point prevalence abstinence at thirty days and six months (primary outcome) post-recruitment; and 3) determine the cost-effectiveness of the nurse-administered, inpatient Tobacco Tactics intervention relative to usual care including cost per quitter, cost per life-year saved, and cost per quality-adjusted life-year saved.

**Methods/Design:**

This effectiveness study will be a quasi-experimental design of six Michigan community hospitals of which three will get the nurse-administered Tobacco Tactics intervention and three will provide their usual care. In both the intervention and usual care sites, research assistants will collect data from patients on their smoking habits and related variables while in the hospital and at thirty days and six months post-recruitment. The intervention will be integrated into the experimental sites by a research nurse who will train Master Trainers at each intervention site. The Master Trainers, in turn, will teach the intervention to all staff nurses. Research nurses will also conduct formative evaluation with nurses to identify barriers and facilitators to dissemination.

Descriptive statistics will be used to summarize the results of surveys administered to nurses, nurses’ participation rates, smokers’ receipt of specific cessation services, and satisfaction with services. General estimating equation analyses will be used to determine differences between intervention groups on satisfaction and quit rates, respectively, with adjustment for the clustering of patients within hospital units. Regression analyses will test the moderation of the effects of the interventions by patient characteristics. Cost-effectiveness will be assessed by constructing three ratios including cost per quitter, cost per life-year saved, and cost per quality-adjusted life-year saved.

**Discussion:**

Given that nurses represent the largest group of front-line providers, this intervention, if proven effective, has the potential for having a wide reach and thus decrease smoking, morbidity and mortality among inpatient smokers.

**Trial registration:**

Dissemination of Tobacco Tactics for Hospitalized Smokers NCT01309217

## Background

Despite strong evidence for the efficacy of inpatient smoking cessation interventions [1], implementation of smoking cessation in hospitals has been limited. Nurses are ideally positioned to provide smoking cessation interventions to inpatient smokers because: 1) nurses are trained in patient education, psychosocial, and physiological interventions; 2) physician time is at a premium while nursing time is more cost-effective; 3) nurses have both access to patients and the opportunity to develop rapport with them as well as the connection to the physicians within the provider team; 4) nurses understand the patient’s medical condition and can tailor the intervention accordingly; and 5) nurses can read charts, initiate medication orders, and write nursing notes. While a meta-analysis showed nurse-administered cessation interventions are efficacious [2], nurse-administered cessation interventions are seldom implemented due to lack of training and time [3].

Over the last 12 years, our team has developed, tested, and refined the efficacious, nurse-administered Tobacco Tactics intervention in multiple populations including head and neck cancer patients [4], veterans [5], and Operating Engineers (ongoing research). In a recent Veterans Affairs (VA) Service Directed Project [5], our team packaged the Tobacco Tactics intervention into a toolkit and trained 573 inpatient nurses and ancillary personnel in two VA hospitals. Preliminary results show that after adjusting for covariates, there was significant improvement in self-reported six-month quit rates for the pre- versus post-intervention time periods in the intervention as compared to the control site. While we are excited about the rapid dissemination and effectiveness of the Tobacco Tactics intervention in the VA, further rigorous testing of implementation outside the VA system is needed. Using six of forty-seven hospitals in the Trinity Health System, the objective of this quasi-experimental study is to compare the implementation of the nurse-administered Tobacco Tactics intervention in three hospitals compared to usual care in three similar hospitals. The specific aims are to: 1) determine provider and patient receptivity, barriers, and facilitators to implementing the nurse-administered, inpatient Tobacco Tactics intervention versus usual care using face-to-face feedback and surveys; 2) compare the effectiveness of the nurse-administered, inpatient Tobacco Tactics intervention versus usual care across hospitals, units, and patient characteristics using thirty-day point prevalence abstinence at thirty days and six months (primary outcome) post-recruitment; and 3) determine the cost-effectiveness of the nurse-administered, inpatient Tobacco Tactics intervention relative to usual care including cost per quitter, cost per life-year saved, and cost per quality-adjusted life-year saved.

Social marketing theory has been used to design and refine the nurse-administered Tobacco Tactics intervention. Social marketing is the planning and implementation of programs designed to bring about social change using concepts from commercial marketing including the ‘4 Ps’: 1) create an enticing ‘Product’ (that is, packaging the Tobacco Tactics intervention into a toolkit for ease of dissemination); 2) minimize the ‘Price’ the target audience believes it must pay, such as offering continuing education units (CEUs) for training, making it easy for nurses to implement and easy for patients to access; 3) make the exchange available in ‘Places’ that reach the audience and fit its lifestyles, such as providing training as part of scheduled nurse training at hospitals on all shifts; and 4) ‘Promote’ the exchange opportunity with creativity and through channels and tactics that maximize desired responses, such as placing a cessation video on the hospital television station and providing a cleverly illustrated, tailored, Tobacco Tactics patient manual enhanced with medications and telephone follow-up [6].

## Methods/Design

### Design

Since many randomized controlled trials have already tested the efficacy of inpatient smoking cessation interventions [1], the real challenge is integrating these interventions into standard of care. Hence, this effectiveness study will use a quasi-experimental design in six Michigan community hospitals of which three will get the nurse-administered Tobacco Tactics intervention and the other three will provide usual care in accordance to how the hospital responds to current Joint Commission (JC) hospital accreditation standards. Implementing the intervention at the facility (hospital) level was the most likely design to remain sustainable once the study was completed.

Throughout the entire study, smokers are surveyed at baseline, thirty days and six months post-recruitment. In this way, quit rates at two time points for all patients are determined during intervention (of less interest), and post-intervention in both the Tobacco Tactics and usual care groups. There are two sources of control. The first source of control is pre- versus post-intervention changes within hospitals; this source of control will NOT control for seasonal changes. The second source of control is changes in the Tobacco Tactics sites compared to the usual care sites; this source of control WILL control for seasonal changes and any other historical events that may influence quit rates across sites.

The quasi-experimental design allows for implementation in natural environments minimizing threats to external validity as natural environments do not suffer the same problems of artificiality as compared to a well-controlled laboratory setting [7]. While quasi-experimental designs are more feasible, the lack of randomization at the patient level may pose many challenges in terms of internal validity making it hard to rule out confounding variables [8]. To minimize the effect of confounding variables, the six hospitals have been split into two groups of three that as a group are matched on hospital size and percentage of minority patients. While we could have arbitrarily decided which group of three hospitals gets the intervention and which does not, we wanted to reduce investigator bias and used a computerized coin flip to assign the groups to experimental and control conditions. See Table 1 for the overall study design.

**Table 1 T1:** Overall study design

**Intervention**	**Pre staff-intervention quit rate**	**Staff-intervention implementation**	**Post staff-intervention quit rate**
Tobacco Tactics	O_1,_ O_2_	X_1_	O_1,_ O_2_
Usual Care	O_1,_ O_2_		O_1,_ O_2_

*O* = Observation (Thirty-day, six-month).

*X* = Intervention.

### Setting and sample

The setting will be six of forty-seven hospitals in the Trinity healthcare system, which is the fourth largest Catholic health-care system in the United States with facilities in nine states. All units will be included, including general medical/surgical, intensive care units/critical care units (ICU/CCU), psychiatric mental health, obstetrics and gynecology (OB/GYN), and pediatrics. The rationale for including all units results from our VA experience where we found exclusion of specific units to be unsuccessful, as specialty units initially excluded (for example, psychiatric mental health and ICU/CCU) felt discriminated against and felt they needed the intervention at least as much as the other units. Moreover, JC standards do not exempt specialty units therefore inclusion of all units is consistent with real world standards. That said, we recognize the need for adaptation of the intervention to specific units such as OB/GYN or pediatrics where the medication component may not be applicable, but the behavioral component would still apply. Including as many units as possible will increase the generalizability of study findings.

Inclusion criteria for the study include inpatients that: 1) are at least 18 years of age; 2) have smoked a cigarette within one month prior to hospitalization; 3) have a projected hospital stay of at least 24 hours; and 4) are willing to complete the questionnaires. The study will exclude inpatients that: 1) refuse to participate; 2) are involved in a concurrent trial that includes a smoking cessation intervention; 3) are non-English speaking (the intervention is currently only in English); 4) are unavailable to participate (for example, never in the room when the research assistant attempts to consent); 5) are not cognitively able to participate; or 6) are not physically able to participate (see Table 2).

**Table 2 T2:** Eligibility criteria

**Inclusion criteria**	
1. at least 18 years of age	
2. smoked a cigarette within one month prior to hospitalization	
3. projected hospital stay of at least 24 hours	
4. willing to complete the questionnaires	
**Exclusion criteria**	
1. refuse to participate	
2. involved in a concurrent trial that includes intervention on smoking	
3. non-English speaking (the intervention is currently only in English)	
4. unavailable to participate	
5. not cognitively able to participate	
6. not physically able to participate	

### Power analysis

The six Trinity sites for the study (three intervention and three control) employ 3,553 inpatient nurses that work across fifty-eight units and discharge 98,350 patients per year (see Table 3). Of the 98,350 annual patients served by the Trinity hospitals, we conservatively estimate that 80% (78,680) of the inpatients will be well enough to participate and, of these, 20% (15,736) will smoke. Based on our previous studies, we anticipate that 50% will agree to participate for a potential recruitment pool of 7,868, which will be more than enough to recruit the 2,350 smokers needed for 80% power to detect a significant difference in cessation rate (the primary outcome) assuming a 30% cessation rate in the intervention group versus 20% in the usual care group, with an alpha of .05. This power analysis was based on the patient as the unit of analysis with attention to clustering by hospital unit. Effects of the clustering on the power of the study were based on intraclass correlation coefficients (ICC) from our preliminary study and the number of clusters in the design. Using the hospital unit as the unit of clustering was justified given that the study is quasi-experimental rather than experimental and that any other analysis would be underpowered.

**Table 3 T3:** Description of six hospital sites

**Group 1**	**RN positions**	**Number of units**	**Annual discharges**	**% minorities**	**Group 2**	**RN positions**	**Number of units**	**Annual discharges**	**% minorities**
Hospital 1	659	11	19,800	70%	Hospital 4	502	12	18,250	31%
Hospital 2	326	9	17,000	4%	Hospital 5	536	8	20,500	29%
Hospital 3	765	9	11,400	27%	Hospital 6	765	9	11,400	48%
**Total**	**1,750**	**29**	**48,200**	**17,618/48,200 = 37%**	**Total**	**1,803**	**29**	**50,150**	**17,075/50,150 = 34%**

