### Data analysis

All analyses that compare the two treatment groups will use the intent-to-treat approach in which patients’ data are analyzed based on the treatment intended, not on the treatment actually received. This approach is taken because it is the best method for evaluating the potential effects of disseminating the Tobacco Tactics intervention, which is our focus. Another implication of this approach is that the approximately 25% of patients who are lost to follow-up are included which assures that differences between conditions are not actually due to differential drop out. Extensive follow-up will be conducted including by telephone to minimize the amount of missing data. Statistically justified imputation methods such as multiple imputation will be used to allow analyses including those who have dropped out.

Analyses will adjust for clustering for patients within units using generalized estimating equations (GEE) analyses. GEE is a method of analysis that can account for the correlations among responses from patients in the same cluster [31]. Given the structure of the study with patients nested within hospital units, the hospital unit will be treated as the cluster. The correlation matrix will be of the exchangeable form, assuming the same correlation among any pair of patients in the same hospital unit. This is standard structuring of the matrix for analyzing clustered non-longitudinal data. Given concerns that GEE might be biased with a small number of units, the adjustment for that factor recommended by Morel [32] will be used for each GEE analysis.

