There is concern that individual hospitals might differ in factors that influence implementation and effectiveness of the intervention. Though the study would be underpowered to use the hospital as the unit of clustering, several strategies will be used to counter the effects of hospital differences on our finding. If there are baseline differences in the type of patients among the six hospitals, we can control for these differences by adding these variables as covariates in the analysis. If there are multiple differences and we are underpowered to add all of these variables as covariates, we will create a propensity score to control for these differences. Note the quit rates and other factors will be assessed in all hospitals before the intervention is conducted in any of them. Comparison of the post-intervention quit rates to the pre-intervention quit rates (and post and pre levels of other outcomes) is built into the analyses.

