We anticipate a quit rate of 30% in the hospitals receiving the Tobacco Tactics intervention and 20% in the usual care hospitals. However, to assure that these differences are not just due to differences between the hospitals, a GEE analysis will be conducted using the logit link function with the hospital unit as the definition of the cluster analogous to moderated logistic regression analysis in which quitting is predicted by time frame (baseline versus intervention period), intervention group (Tobacco Tactics versus usual care), and the product of those two variables. The statistical significance of the product will indicate that the difference between the Tobacco Tactics and the usual care comparison sites depends on whether or not the intervention has been implemented. We anticipate no difference between the sites at baseline, but a notable difference after the interventions have been implemented.

In addition, harm reduction will be compared between the two groups by analyses of number of cigarettes smoked per day, number of quit attempts, and nicotine dependence (as indicated by Fagerstrom test). For each of these analyses, the same general approach taken to the primary dependent variable will be applied including: descriptive statistics on baseline and intervention period and a GEE with the hospital unit as the definition of the cluster analogous to moderated regression analysis to compare the differences between the sites (Tobacco Tactics versus usual care) by time (baseline versus intervention period). Both the descriptive statistics and the significance tests differ for these other outcome measures because of their different distributions (that is, normal or not). Count variables will be analyzed assuming a Poisson distribution using a log link function while the Fagerstrom test scores will be modeled with an identity link function since it is normally distributed.

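### The intervention is assigned and delivered by hospital (three against three), but the primary time-by-group product is tested with 58 units as independent clusters, so hospital-specific change over time is largely missing from its standard error

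*Protocol article*

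**What the plan says.** **Assignment and delivery (Design).** On the grouping: "the six hospitals have been split into two groups of three that as a group are matched on hospital size and percentage of minority patients". The investigators then "used a computerized coin flip to assign the groups to experimental and control conditions". Delivery is also by hospital: "Implementing the intervention at the facility (hospital) level was the most likely design to remain sustainable once the study was completed".

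**Analysis (Data analysis).** "Given the structure of the study with patients nested within hospital units, the hospital unit will be treated as the cluster". The GEE uses an exchangeable correlation and Morel's small-sample adjustment for the number of units. Under Aim 2, the primary test is the product of time frame and intervention group in a logit GEE with the unit as cluster.

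**Rationale (Power analysis).** The six sites "employ 3,553 inpatient nurses that work across fifty-eight units". The stated reason for this choice is "Using the hospital unit as the unit of clustering was justified given that the study is quasi-experimental rather than experimental", together with the remark that any alternative would lack power. The Data analysis section repeats the second reason: "Though the study would be underpowered to use the hospital as the unit of clustering". It voices concern that hospitals may differ in factors affecting implementation and effectiveness. Its answer is patient covariates, or a propensity score, plus the pre/post comparison.

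**Claim for the result (Aim 2).** The unit-clustered GEE is presented as the means "to assure that these differences are not just due to differences between the hospitals".

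**The concern.** Anything that changes between the two periods at one hospital moves all of its 8 to 12 units together. The protocol describes several routes for this. Master Trainers work by site. Training takes two to six months, depending on how far the hospital can release its nurses. Modifications to implementation are expected to vary by unit and hospital. Usual care depends on how each hospital responds to accreditation standards. An analysis clustered on units counts such a shared change as if it had arisen separately in each unit.

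The two reasons in the Power analysis section do not bear on this. A quasi-experimental label does not alter the level at which treatment was assigned. Low power at that level is a limitation to report and gives no ground for a smaller standard error. The planned safeguards do not reach the problem either:
- Covariates and the propensity score adjust for measured patient mix.
- The pre/post contrast removes only stable differences.
- The concurrent control group covers events common to all sites.
- Morel's adjustment concerns the number of units, not six hospitals.

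At stake is the primary conclusion: a change peculiar to one or two hospitals could be declared an intervention effect.

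**Working it through.** **1. The plan's own sample size.** For 30% v 20%, two-sided 5% and 80% power, the unclustered requirement is 294 per arm, 588 in all. The stated 2,350 is 2,350/588 = 4.00 times that. The article does not print the ICC behind it, so 2,350 cannot be recomputed. That is not held against the article and plays no part below.

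**2. Inputs.**
- Units (Table 3): 11 + 9 + 9 = 29 and 12 + 8 + 9 = 29, in 3 v 3 hospitals.
- Outcomes: 2,350 × 0.75 ≈ 1,762, using the roughly 25% loss to follow-up given under Data analysis; four equal arm-by-period cells of 440.5 (assumed equal).
- Quit rates: 20% in three cells and 30% in the fourth.
- Hospital-by-period SD, s, on the logit scale: **not in the documents; assumed**, 0 to 0.3. At a 20% quit rate, 0.1 logit is about 0.1 × 0.16 = 1.6 percentage points, and 0.2 is about 3.2.
- Unit-by-period variation: set to zero at first.

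**3. Variance of the product (log odds ratio).**

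Sampling part: v0 = 3/(440.5 × 0.16) + 1/(440.5 × 0.21) = 0.0426 + 0.0108 = 0.0534.

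Hospital part: each hospital's change has variance 2s². Averaging three hospitals gives 2s²/3, and the difference between arms has 4s²/3. Hence

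- true variance = v0 + 4s²/3
- variance seen by unit clustering ≈ v0 + 4s²/29
- type I error = 2Φ(−1.96 × √(seen/true))

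| s (logit) | True variance | Seen | SE ratio | Type I error |
|---|---|---|---|---|
| 0 | 0.0534 | 0.0534 | 1.00 | 5.0% |
| 0.05 | 0.0567 | 0.0537 | 0.97 | 5.6% |
| 0.1 | 0.0667 | 0.0548 | 0.91 | 7.6% |
| 0.2 | 0.1067 | 0.0589 | 0.74 | 14.5% |
| 0.3 | 0.1734 | 0.0658 | 0.62 | 22.7% |

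**4. Sensitivity.** Unit-by-period variation with SD u adds 4u²/29 to both variances. At s = 0.2, type I error falls from 14.5% to 12.9% (u = 0.3) or 11.1% (u = 0.5). Taking v0 under the null instead (all cells at 20%, v0 = 0.0568) gives 7.4%, 14.0% and 22.0% at s = 0.1, 0.2 and 0.3.

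**5. Simulation.** This used 58 units in the Table 3 pattern, about 20 patients per unit and period, a stable hospital SD of 0.3 logit, a unit-by-period SD of 0.1, and 4,000 runs. A t-test on unit changes stood in for the GEE. At s = 0, 0.1, 0.2 and 0.3 the unit-level test rejected a true null in 4.7%, 8.5%, 17% and 26% of runs. A t-test on the six hospital changes (4 df) stayed at 4.4% to 5.1%. The 4.7% at s = 0 confirms that stable hospital differences cancel.

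**6. Power of hospital-level inference.** The effect is log(0.3/0.7) − log(0.2/0.8) = 0.539. With 4 df (critical value 2.776):
- s = 0: non-centrality 0.539/√0.0534 = 2.33, power about 43%.
- s = 0.2: 0.539/√0.1067 = 1.65, power about 25%.

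**The case against.** **The harm is conditional, and partly anticipated.** The protocol gives no hospital-by-period variance. At zero the unit-level test is nominal, at 0.05 logit it is barely off, and real unit-by-period variation would dilute the inflation. The authors disclose both the choice and its power motive, name hospital differences as a concern, and plan adjustment for measured case mix. They will also report quit rates by hospital, with both periods assessed in every hospital. All of this stands. It limits the size of the problem but does not make the stated rationale correct.

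**The Aim 2 assurance can be read charitably.** It comes from the product with its baseline contrast, and for stable hospital differences that works. It does not extend to a change specific to one hospital.

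**Hospital-level inference is weak and not strictly design-based.** Power of 25% to 43% is a heavy price. One flip between two fixed groups gives only two possible assignments, so a 3 v 3 t-test also rests on a model. This stands as a reason to set the hospital-level analysis beside the GEE instead of substituting it.

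**Stronger readings that a reader might infer.** One is that the standard error omits all hospital-level variation. It does not: stable differences cancel, and a small part of the hospital-by-period component is captured through the spread between units. Another is that the uneven minority shares in Table 3 (70/4/27% v 31/29/48%) show the standard error to be wrong. They describe stable differences and say nothing about variation in change.

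**Conclusion.** The mismatch is real. Treatment is assigned and delivered by hospital, inference counts units, and neither reason given makes units of one hospital independent. The affected component is hospital-by-period variation. The nominal 5% holds only if that is negligible, an assumption the protocol does not state and its own concern about hospital differences undercuts.

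The inflation runs from none to about 23% over the assumed range of 0 to 0.3 logit, on 1,762 outcomes in equal cells without unit-by-period variation. It would be tempting to conclude flatly that the primary p-values and intervals are too optimistic. The documents do not support that, because they contain no estimate of this SD. What they support is that the unit-level result alone cannot separate an intervention effect from hospital-specific change, and that the Aim 2 wording promises more than the analysis delivers.

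**What to change.** 1. Keep the unit-level GEE.
2. Prespecify beside it a hospital-level analysis: the pre-to-post change in log-odds of quitting for each of the six hospitals, compared 3 v 3 with a t-test on 4 df, or an equivalent hospital-by-period random effect.
3. Report both intervals and the six hospital-specific changes.
4. In the Power analysis section, replace the justification for unit clustering, and under Aim 2 replace the assurance about hospital differences. State instead that the unit-level p-value and the 80% power assume no hospital-by-period variation.
5. Claim an effect beyond hospital-specific change only as far as the hospital-level interval supports it.

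Adding hospital fixed effects to the GEE would not serve, since they remove stable differences that the product already removes.

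**Cost.** One extra analysis on data already planned, and changed wording. The real price is a wider second interval, with power of about 43% for 20% v 30% at SD 0 and 25% at SD 0.2, and a more modest conclusion.
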